#### Table 2 Primary and secondary objectives and research questions

1. **Primary objective and research question**

| **Objective:** | To compare overall survival (OS) in patients > 18 years with metastatic [organ]carcinoma with a biomarker Y+ mutation who have shown progression after first line treatment and have indicated informed consent for longitudinal observational data collection as part of the XYZ Registry and are treated with a combination of Drug A and Drug B compared to controls who are treated with standard care for a period of a maximum of 2 years (or 4 years). Comparator patients will be included retrospectively as well prospectively. |
| --- | --- |
| **Hypothesis:** | Overall survival will be improved with Drug A and Drug B compared to standard of care. |
| **Population *(mention key inclusion-exclusion criteria):*** | Patients with biomarker Y+ positive metastatic [organ] cancer who progressed after at least of one line of treatment |
| **Exposure:** | Initiation of Drug A in combination with Drug B |
| **Comparator:** | Standard of care. In [anonymous country], SoC second line therapy is Drug C or in third line the SoC is Drug D. There will be 2 comparator arms. One will be initiation of Drug C or Drug D using concurrent years of data with the exposure arm. The other comparator group will be initiatiors of Drug C or Drug D using historical controls from years of data prior to availability of Drug A/B. |
| **Outcome:** | Overall Survival (OS) |
| **Time *(when follow up begins and ends):*** | Follow up from day after initiation of therapy until the first of outcome, discontinuation, add/switch therapy, disenrollment, end of study period, nursing home admission, death, progression of therapy, others to be discussed. |
| **Setting:** | Outpatient care |
| **Main measure of effect:** | Hazard Ratio (to be discussed). |

1. **Secondary objective 1 and research question**

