| **Objective:** | To compare toxicity and/or adverse effects in patients > 18 years with metastatic [organ]carcinoma with a biomarker Y+ mutation who have shown progression after first line treatment and have indicated informed consent for longitudinal observational data collection as part of the XYZ Data Registry and are treated with a combination of Drug A/B compared to patients who are treated with standard care for a period of a maximum of 2 years (or 4 years). Comparator patients will be included retrospectively as well prospectively. |
| --- | --- |
| **Hypothesis:** | Toxicity and/or adverse effects will be no different with Drug A and Drug B compared to standard of care. |
| **Population *(mention key inclusion-exclusion criteria):*** | Patients with biomarker Y+ positive metastatic [organ] cancer who progressed after at least of one line of treatment |
| **Exposure:** | Initiation of Drug A in combination with Drug B |
| **Comparator:** | Standard of care. In [anonymous country], SoC second line therapy is Drug C or in third line the SoC is Drug D. There will be 2 comparator arms. One will be initiation of Drug C or Drug D using concurrent years of data with the exposure arm. The other comparator group will be initiatiors of Drug C or Drug D using historical controls from years of data prior to availability of Drug A/B. |
| **Outcome:** | Toxicity and/or adverse effects |
| **Time:** | Follow up from day after initiation of therapy until the first of outcome, discontinuation, add/switch therapy, disenrollment, end of study period, nursing home admission, death, progression of therapy, others to be discussed. |
| **Setting:** | Outpatient care |
| **Main measure of effect:** | Hazard ratio (to be discussed) |

1. **Secondary objective 4 and research question**

| **Objective:** | To compare resource use in patients > 18 years with metastatic [organ]carcinoma with a biomarker Y+ mutation who have shown progression after first line treatment and have indicated informed consent for longitudinal observational data collection as part of the XYZ Data Registry and are treated with a combination of Drug A/B compared to patients who are treated with standard care for a period of a maximum of 2 years (or 4 years). Comparator patients will be included retrospectively as well prospectively |
| --- | --- |
| **Hypothesis:** | Resource utilization will be reduced with Drug A and Drug B compared to standard of care. |

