| **Population *(mention key inclusion-exclusion criteria):*** | Patients with biomarker Y+ positive metastatic [organ] cancer who progressed after at least of one line of treatment |
| **Exposure:** | Initiation of Drug A in combination with Drug B |
| **Comparator:** | Standard of care. In [anonymous country], SoC second line therapy is Drug C or in third line the SoC is Drug D. There will be 2 comparator arms. One will be initiation of Drug C or Drug D using concurrent years of data with the exposure arm. The other comparator group will be initiatiors of Drug C or Drug D using historical controls from years of data prior to availability of Drug A/B. |
| **Outcome:** | Resource utilization |
| **Time:** | Follow up from day after initiation of therapy until the first of outcome, discontinuation, add/switch therapy, disenrollment, end of study period, nursing home admission, death, progression of therapy, others to be discussed. |
| **Setting:** | Outpatient care |
| **Main measure of effect:** | Descriptive statistics (to be discussed) |

1. Research methods
   1. Study design

**Research design (e.g. cohort, case-control, etc.):** New user active comparator cohort study

**Rationale for study design choice:** In order compare the new treatment (Drug A/B) with standard of care (SoC), patients need to be followed from start treatment until censoring (death, progression, treatment failure, end of follow-up). Use of this design will help prevent time related biases such as depletion of susceptible, immortal time bias and adjustment for causal intermediates.

- 1. Study design diagram

[figure not shown]

- 1. Setting

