**Algorithm to define duration of exposure effect:**

If a refill occurs before the end of days supply dispensed, add overlapping days to the end of the subsequent dispensing’s day supply. Assume that the effect of a pill lasts for 30 days. Therefore, we allow up to a 30 day gap between a dispensation + days supply and refill. We also add 30 days to the last dispensation + days supply in a treatment episode and consider this “exposed” time.

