#### 7.4.3 Context and rationale for follow up

For the primary outcome of death and secondary outcomes of progression free survival and toxic adverse side effects, we will implement an on-treatment follow up analysis with censoring as defined in table 6. For health-related quality of life outcomes, we will use panel measurements in accordance with the XYZ registry’s data collection schedule. Details of the analyses for health-related quality of life outcomes will be determined after further discussion.

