#### Table 8. Operational Definitions of Follow Up

|  |  |  |  |
| --- | --- | --- | --- |
| **Follow up start** | Day 1 |  |  |
| **Follow up end^1^** | **Select all that apply** |  | **Specify** |
| **Date of outcome** | Yes |  | See Table 5 |
| **Date of death** | Yes |  | Discharged dead or registry recorded death, whichever came 1st |
| **End of observation in data** | Yes |  | Allow 30 day gaps in enrolment |
| **Day X following index date**  *(specify day)* | Yes |  | Day 365 |
| **End of study period**  (specify date) | Yes |  | 30-Sep-15 |
| **End of exposure**  *(specify operational details,*  *e.g. stockpiling algorithm, grace period)* | Yes |  | **Stockpiling algorithm:** If refill occurs before end of days supply, count overlapping days at the end of the subsequent dispensing’s day supply.  **Grace period:** Bridge gaps of ≤30 days between dispensation + days supply and refill. Add 30 days to last dispensation + days supply in a treatment episode. |
| **Date of add to/switch from exposure**  *(specify algorithm)* | Yes |  | Date that patient in exposed group is dispensed comparator drug or vice versa |
| **Other date** *(specify)* | Yes |  | Nursing home admission |

^1^ Follow up ends at the first occurrence of any of the selected criteria that end follow up.

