#### Table 12. Metadata about data sources and software

|  | **Data 1** | **Data 2** |
| --- | --- | --- |
| **Data Source(s):** | XYZ Data Registry (concurrent/prospective) | XYZ Data Registry (historical) |
| **Study Period:** | Jan 1, 2021- Dec 31, 2022 | Jan 1, 2019- Dec 31, 2020 |
| **Eligible Cohort Entry Period:** | Jan 1, 2021- Dec 31, 2022 | Jan 1, 2019- Dec 31, 2020 |
| **Data Version (or date of last update):** | V2.0 – V5.0 | V1.0 |
| **Data sampling/extraction criteria:** | All patients > 18 years with metastatic [organ] carcinoma with a biomarker Y+ mutation who have shown progression after first line treatment and are treated with a combination of Drug A/B or with standard care | All patients > 18 years with metastatic [organ] carcinoma with a biomarker Y+ mutation who have shown progression after first line treatment and are treated with standard care |
| **Type(s) of data:** | Patient registry data including linked electronic health records, insurance claims, death, and patient reported outcomes | Patient registry data including linked electronic health records, insurance claims, death, and patient reported outcomes |
| **Data linkage:** | Linked based on universal patient identifier in [anonymous country] | Linked based on universal patient identifier in [anonymous country] |
| **Conversion to CDM*:** | n/a | n/a |
| **Software for data management:** | SAS 9.4, My SQL 15.0.2000.5 | SAS 9.4, My SQL 15.0.2000.5 |

*CDM = Common Data Model

- 1. Data management

The research team operates a secure, state-of-the-art, computing facility. The computer cluster is Linux-based and offers SAS 9.4, Stata 15.1, and R. The data center is a secure facility that houses both our computing environment as well as clinical systems and electronic medical records for several large hospitals in WA. Entry into the computer room requires passing through staffed building security, a successful palm scan, and then passing through staffed computer room security. The research machines are connected to the networking backbone with 10 gigabit-per-second fiber links. Network security is overseen by Information Security, who apply the same standards used for the hospitals electronic medical records systems to the research teams data. All data are transmitted to programmers' workstations in an encrypted state. Backups are created using 256-bit AES encryption, the current Department of Defense standard for data security, and are stored in a locked facility.

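### Overall survival and toxicity: section 7.1 and Table 2 name progression-type ends of follow-up that Table 8, the operational list, does not

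*Protocol*

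**What the plan says.** Four places in the protocol bear on when follow-up ends.

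- **Section 6, Table 2 (Time row, the same for all five objectives).** After the outcome itself, the ends are "discontinuation, add/switch therapy, disenrollment, end of study period, nursing home admission, death, progression of therapy". The row closes with "nursing home admission, death, progression of therapy, others to be discussed", so only further, unnamed ends are left for discussion.
- **Section 7.1 (rationale for the design).** It states that "patients need to be followed from start treatment until censoring (death, progression, treatment failure, end of follow-up").
- **Section 7.4.3.** For death, PFS and "toxic adverse side effects, we will implement an on-treatment follow up analysis with censoring as defined in table 6". In Table 6 the assessment window of each row runs from day 1 to an undefined censoring point.
- **Table 8.** It selects eight ends, and its footnote gives the rule: "Follow up ends at the first occurrence of any of the selected criteria that end follow up". Progression and treatment failure are not among the eight. A switch is defined as "Date that patient in exposed group is dispensed comparator drug or vice versa".

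Section 7.4.1 fixes what counts as exposed: "We also add 30 days to the last dispensation + days supply in a treatment episode and consider this “exposed” time". Nothing in that algorithm makes progression end exposure.

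Table 8 also gives 30-Sep-15 as the end of the study period. In Table 12 the earliest cohort entry period is "Jan 1, 2019- Dec 31, 2020".

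**The concern.** Two analysts could each follow a different part of this protocol faithfully and obtain different follow-up for the same patients. One, working from section 7.1, would censor an overall survival or toxicity record at progression. The other, working from Table 8, would continue to the end of exposure, a switch or another listed end.

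The difference falls on time the protocol itself calls exposed, so the first reading works against the on-treatment analysis of section 7.4.3. Deaths and toxic events soon after progression would be lost. Progression is also related to prognosis, and the first secondary objective expects PFS or time to treatment failure to be better on Drug A/B. Censoring there could therefore be informative and could act at different times in the two arms.

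**Working it through.** **1. The plan's only related figure.** Section 7.9 claims more than 80% power for a hazard ratio of 0.90, with about 5,000 exposed patients matched 1:1 and 35% deaths. This gives 10,000 × 0.35 = 3,500 deaths. With two-sided alpha 0.05 (assumed from the 95% interval), Schoenfeld's formula gives power = Φ(|ln 0.90| × √3,500 / 2 − 1.96) = Φ(3.117 − 1.960) = 87.6%. The claim reproduces, and the present point does not depend on it.

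**2. The lists side by side.**

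| End of follow-up | Table 2 | Section 7.1 | Table 8 |
|---|---|---|---|
| Outcome | yes | – | yes |
| Death | yes | yes | yes |
| End of study period | yes | general end of follow-up | yes |
| Nursing home admission | yes | – | yes |
| Discontinuation / end of exposure | yes | – | yes, with 30 days added |
| Disenrolment / end of observation | yes | – | yes |
| Add or switch | yes, unrestricted | – | only between exposure and comparator groups |
| Progression | yes, ambiguous | yes | **no** |
| Treatment failure | – | yes | **no** |
| Day 365 | – | – | yes |

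Table 2 and Table 8 share four ends by name. Two more match if discontinuation means end of exposure and disenrolment means end of observation. Add/switch matches only in part: a move from Drug C to Drug D is a switch in Table 2's plain wording, but both drugs belong to the comparator group, so it is not a switch in Table 8.

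**3. The two readings of the Table 2 phrase.** If it means disease progression, Table 2 and section 7.1 both conflict with Table 8. If it means moving to the next line of treatment, Table 2 largely overlaps with add/switch, but section 7.1 still names progression and treatment failure, so it still conflicts with Table 8.

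**4. The pointers.** Section 7.4.3 cites Table 6 where the list is in Table 8. Table 8's outcome row cites Table 5 (exclusion criteria) where outcomes are in Table 7. Both references are low by two, which suggests a numbering slip.

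**5. Effect by outcome.**

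- *Overall survival and toxicity:* ending at progression removes events between progression and the first Table 8 end. Events after that Table 8 end are lost under either list.
- *PFS/TTTF:* progression or treatment failure is the outcome, so Table 8 also stops there. What remains is whether it is an event (Table 8) or censoring (section 7.1).
- *Quality of life and resource use:* section 7.4.3 uses the registry's panel schedule for the first, and the models for both are deferred. The effect is open.

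**6. Upper bound on the time at stake per patient (overall survival or toxicity).** Let c be the days of supply left at progression, with no later refill, and s the days to a Table 8 switch. Time lost is at most min(c + 30, s); any other Table 8 end shortens it. The protocol gives neither c nor s, so these values are assumed.

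| | s = 0 | s = 14 | no switch |
|---|---|---|---|
| c = 0 | 0 | 14 | 30 |
| c = 28 | 0 | 14 | 28 + 30 = 58 |

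If Table 8 governs, nothing is lost at progression.

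**7. Table 8's study end.** 30 September 2015 lies more than three years before the earliest entry date, 1 January 2019. Under the first-occurrence rule, read literally, follow-up would end before time 0 for every patient.

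**The case against.** The strongest reply is that Table 8 is plainly the governing list. It is titled as the operational definition, sits under section 7.4.3 and states its own stopping rule. Section 7.1 is one sentence of design rationale. It even calls death censoring, which cannot be meant literally for overall survival. The Table 6 reference looks like a slip. The document is also an openly unfinished version, and section 8 already promises sensitivity analyses on reasons for censoring and censoring weights.

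Much of this stands. It settles which list should win and makes the pointer a small error. It does not remove the contradiction. Progression is stated as an end in section 7.1 without any mark that it is undecided, and in Table 2 only the additional ends are left open. Sensitivity analyses do not decide the primary rule, and Table 11 is still blank. Nor can Table 8 simply be applied as it stands, because its study end is impossible.

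A reader might infer that the conflict affects all five objectives, since Table 2 repeats the same row. The documents do not support that. For PFS/TTTF progression is already the outcome, and the analyses of quality of life and resource use are deferred. A reader might also infer that the toxicity hazard ratio is biased in a known direction. That does not follow either: a Cox model treats the shorter follow-up as censoring, and the protocol gives no progression times, supply lengths or toxicity rates.

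**Conclusion.** The point holds for overall survival and toxicity. Section 7.1, and Table 2 if its phrase means disease progression, end follow-up at something Table 8 does not list. Following them would drop deaths and toxic events in time the protocol counts as exposed.

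The mismatch in wording is certain. The consequence is conditional on an analyst following section 7.1 or that reading of Table 2. The 0 to 58 days shown are upper bounds on assumed supply and switch times, not estimates. Informative, arm-dependent censoring is possible given the plan's own expectation for PFS/TTTF, but its size and direction cannot be derived. This should be corrected before registration; it does not call the design into question.

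**What to change.** 1. State that Table 8 governs. Correct the section 7.4.3 pointer from Table 6 to Table 8, and Table 8's outcome pointer from Table 5 to Table 7.
2. Replace 30-Sep-15 with a study end consistent with Table 12.
3. For overall survival and toxicity, delete progression and treatment failure as censoring ends in section 7.1 and Table 2. For PFS/TTTF, say that they are events.
4. State that toxicity follow-up runs to the end of exposure in Table 8, including the added 30 days, regardless of progression and subject to the other Table 8 ends.
5. If the Table 2 phrase means the next line of treatment, move it to the Table 8 switch row and say whether Drug C to Drug D counts.
6. When aligning Table 2 with Table 8, reconcile day 365 with the maximum of two (or four) years in the Table 2 objectives. Copying day 365 across without this would create a new conflict.

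The cost is wording in Table 2, Table 8 and sections 7.1 and 7.4.3. One small downside remains: some late toxic events may reflect the advancing disease rather than the drug.

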# 1. Title Page

DISCLAIMER: This protocol is based on the research question and design from a real study protocol under development. It has been anonymized due to the ongoing nature of the work. To reflect the realistic situation of a developing protocol with multiple versions after input from various stakeholders, at several points in the document, the protocol states that a decision is “to be discussed” or “to be determined” indicating that it will be further developed in a later version of the protocol. Abbreviated responses are provided to illustrate how to use the protocol template, however appendices were not prepared for this example protocol.

| Title | Drug A/B combination as a second- or third-line treatment of patients with biomarker Y+ metastatic cancer compared to usual standard care |
| --- | --- |
| Research question & Objectives | The objective is to evaluate the comparative effectiveness and cost-effectiveness of Drug A/B as a second- or third-line treatment of patients with biomarker Y+ metastatic colorectal cancer compared to standard care |
| Protocol version | V1 |
| Last update date | 2021-10-26 |
| Contributors | **Primary investigator contact information:**  [contact]  **Contributor names:**  [name]  [name] |
| Study registration | **Site:** Health Technology Assessment of Anonymous Country  **Identifier:** To Be Determined |
| Sponsor | **Organization:** Health Technology Assessment of Anonymous Country  **Contact:** [contact] |
| Conflict of interest | n/a |

Table of contents

[1. Title Page 1](#_Toc102631400)

[2. Abstract 3](#_Toc102631401)

[3. Amendments and updates 4](#_Toc102631402)

[4. Milestones 5](#_Toc102631403)

[Table 1 Milestones 5](#_Toc102631404)

[5. Rationale and background 5](#_Toc102631405)

[6. Research question and objectives 6](#_Toc102631406)

[Table 2 Primary and secondary objectives and research questions 6](#_Toc102631407)

[7. Research methods 10](#_Toc102631408)

[7.1. Study design 10](#_Toc102631409)

[7.2. Study design diagram 11](#_Toc102631410)

[7.3. Setting 11](#_Toc102631411)

[7.3.1 Context and rationale for definition of time 0 (and other primary time anchors) for entry to the study population 11](#_Toc102631412)

[Table 3 Operational Definition of Time 0 (index date) and other primary time anchors 11](#_Toc102631413)

[7.3.2 Context and rationale for study inclusion criteria: 12](#_Toc102631414)

[Table 4. Operational Definitions of Inclusion Criteria 12](#_Toc102631415)

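### Resource use is given the on-treatment stop list written for survival outcomes, so later use is cut off, and cut off unequally if the arms differ in time on treatment or to progression

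*Protocol*

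**What the plan says.** Table 2, secondary objective 4, takes resource utilization as its outcome and states the hypothesis "Resource utilization will be reduced with Drug A and Drug B compared to standard of care". Its Time row follows patients "until the first of outcome, discontinuation, add/switch therapy, disenrollment, end of study period, nursing home admission"; in full, the stops listed after the outcome are "discontinuation, add/switch therapy, disenrollment, end of study period, nursing home admission, death, progression of therapy, others to be discussed". The same row appears under overall survival, progression-free survival, quality of life and toxicity. The objective describes care "standard care for a period of a maximum of 2 years (or 4 years", and the effect measure is "Descriptive statistics (to be discussed".

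Section 7.1 explains the design by saying that "patients need to be followed from start treatment until censoring (death, progression, treatment failure, end of follow-up").

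Section 7.4.3 assigns follow-up by outcome. For death and the "secondary outcomes of progression free survival and toxic adverse side effects, we will implement an on-treatment follow up analysis". Quality of life gets panel measurements instead. Resource use is not mentioned.

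Table 8 ends follow-up at the earliest of: outcome, death, end of observation, Day 365, end of study period, end of exposure plus 30 days, switch or addition, and nursing home admission. It has no progression row, and its footnote is not limited to particular outcomes.

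Table 7 leaves the type of the resource-use outcome open, and section 7.5.1 defers its model. The title page states the aim as the "comparative effectiveness and cost-effectiveness of Drug A/B".

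**The concern.** A stop list for a time-to-event outcome says when a patient is no longer at risk of a first event under the treatment studied. Resource use is a sum over time, and the list does not suit it in three ways.

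- Stopping at the outcome has no useful meaning for a sum. Taken literally, the count ends at the first resource used.
- Nursing home admission is arguably resource use itself, yet it closes the count.
- Stopping at discontinuation, switch or progression leaves out later-line and end-of-life care.

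How much is left out depends on how soon each patient reaches a stop event. Those events are related to treatment and prognosis, and the protocol expects the arms to differ on them: secondary objective 1 hypothesises better progression-free survival or time to treatment failure with Drug A/B. A difference in observed use would then mix a difference in use with a difference in length of observation. Totals of this kind are a poor basis for cost-effectiveness.

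**Working it through.** **The plan's own figure.** The only calculation in the protocol is the power for overall survival in section 7.9. It reproduces: 10,000 matched patients x 0.35 = 3,500 deaths; sqrt(3,500 x 0.25) x |ln 0.90| = 3.12; 3.12 - 1.96 = 1.16, or 87.6% power, against more than 80% stated. It has no bearing on resource use, for which the protocol gives no figure.

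**Illustration: assumed inputs.** None of these is in the documents.
- Time to progression is exponential with median m months, rate L = ln 2/m. Pairs (A/B v SoC): 5 v 4, 6 v 4, 6 v 3, and 3 v 4 as a reverse case.
- Death occurs only after progression, at rate M = ln 2/5 per month.
- Use per month is 1 unit before progression in both arms and c = 0.5, 1 or 2 after it, with k = 0 or 3 units at death.
- The horizon is 12 months, as with Day 365 in Table 8.

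**Formulas.**
- Months before progression: P = (1 - e^(-12L))/L.
- Progressed and alive at month 12: B = L e^(-12M) (1 - e^(-12(L-M)))/(L-M).
- Dead by month 12: D = 1 - e^(-12L) - B.
- Months alive after progression: Q = D/M.
- Truncated total = P. Complete total = P + cQ + kD.

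**Components.**

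| Median (months) | P | Q | D |
|---|---|---|---|
| 3 | 4.06 | 4.47 | 0.620 |
| 4 | 5.05 | 3.99 | 0.553 |
| 5 | 5.85 | 3.57 | 0.495 |
| 6 | 6.49 | 3.23 | 0.447 |

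**Ratios of per-patient totals, A/B to SoC.**

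| Medians | Truncated | Complete, over all c and k |
|---|---|---|
| 5 v 4 | 5.85/5.05 = 1.16 | 0.99 to 1.08 |
| 6 v 4 | 6.49/5.05 = 1.29 | 0.97 to 1.15 |
| 6 v 3 | 6.49/4.06 = 1.60 | 0.96 to 1.29 |
| 3 v 4 | 4.06/5.05 = 0.80 | 0.89 to 1.01 |

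Example, 6 v 4 with c = 1 and k = 0: (6.49 + 3.23)/(5.05 + 3.99) = 9.72/9.04 = 1.08.

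**Share of 12-month use lost.** It runs from 20% (median 6, c = 0.5, k = 0: 1 - 6.49/8.11) to 73% (median 3, c = 2, k = 3: 1 - 4.06/14.86).

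**Per month of follow-up.** The truncated ratio is 1.00 throughout, because monthly use before progression was set equal. The complete ratio for the first three pairs runs from 0.84 to 1.13.

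**Break-even.** In the 6 v 4 case the truncated ratio falls below 1 if monthly use before progression with A/B is below 5.05/6.49 = 0.78 of that with SoC.

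**Check against 35% mortality.** The inputs imply one-year mortality of 45% to 62% (column D), above the 35% in section 7.9. Choosing M so that D = 0.35 in the SoC arm gives median survival after progression of 10.3 months (SoC median 4) or 12.2 months (SoC median 3). The complete ratios for the first three pairs then run from 0.91 to 1.21. The truncated ratios do not change.

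**The case against.** The strongest reply is that little here is settled. The stop list itself ends by leaving further items open, and the outcome type, effect measure and model for resource use are all still to be discussed. The Time row is repeated text: quality of life carries the same row, yet section 7.4.3 replaces it with panel measurements. Silence on resource use may mean that its window is undecided. This lowers the severity but does not remove the point. The open items are the measure and the model; the stop events are written down, and nothing in section 7.4.3 or Table 8 overrides them for resource use.

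A reader might infer that Drug A/B will look more expensive. The documents do not support that. It needs cumulative per-patient totals and similar monthly use, and neither is specified. Lower use with A/B is the protocol's own hypothesis, and earlier discontinuation of A/B would push the other way. Objective 4 also concerns resource use; no cost analysis is specified.

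A reader might also take tumour progression as a settled stop. Table 2 speaks of progression of the therapy, which could mean a change of line, and Table 8 has no such row. Section 7.1 favours the tumour reading. Discontinuation and switch truncate the count under either reading. Nor is anyone likely to stop counting at the first resource used; that reading only shows that the row was not written for this outcome.

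Section 8 acknowledges informative censoring and plans sensitivity analyses and censoring weights. These are not tied to resource use. Weighting for discontinuation would also estimate use as if patients never stopped, not the use they incur.

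**Conclusion.** The point holds in a limited form. As written, objective 4 and Table 8 truncate resource use at events related to treatment and prognosis, and the truncation is unequal if the arms differ in time on treatment or to progression. This does not suit the cost-effectiveness aim.

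The size is illustrative only. If per-patient totals are compared and monthly use before progression is equal, the arm observed longer appears to use about 16% to 60% more, against -4% to +29% with complete follow-up. These ranges rest wholly on assumed progression times, survival after progression and use rates, and they model a stop at progression only, not discontinuation with the 30-day grace period. Reporting per observed month removes the spurious excess but cannot show any difference after progression. The direction of bias in the real data cannot be stated from the documents.

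The objective is secondary and the protocol is an early draft, so this should be corrected before the resource-use analysis is written. It does not affect the primary analysis.

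**What to change.** Give objective 4 its own follow-up rule. Count all in-scope resource use from Day 1 to death, disenrolment, end of data or one common fixed horizon, regardless of discontinuation, switch, progression or nursing home admission. State whether nursing home care is in scope, since the setting is given as outpatient. Handle administrative censoring with a method for censored cumulative use, and report use per month alive as well as the total per patient. An on-treatment summary can remain as a supplement.

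Make the change in Table 2, section 7.4.3 and Table 8 together; changing Table 2 alone would leave it in conflict with Table 8.

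Reconcile the horizon too: Day 365 in Table 8 against 2 (or 4) years in the objective. Table 12 gives a study period of 730 days (1 January 2021 to 31 December 2022) with entry open to the last day. As it stands, four years cannot be observed in the concurrent data, and if entry were uniform only about half the patients (365/730) could reach Day 365. The end-of-study date in Table 8, 30-Sep-15, precedes all the data and needs correcting in the same edit.

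The cost is edits in three places and somewhat more analysis work. Table 12 already lists linked claims and death records, so no new data source should be needed for the use they capture.
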